### **Hand grip strength**

Hand grip strength will be measured in kilogram using a hand-held dynamometer with three attempts to assess physical fitness that related to muscular strength. The peak pressure of each 5-second attempt and the highest value will be recorded [49]. This hand-held dynamometer has excellent reliability (ICC = 0.98) and construct validity of  $r = 0.99$  (very high correlation) with Rolyan dynamometers [50].

### **EuroQol (EQ-5D-5L)**

Health related quality of life will be evaluated using self-assessment questionnaire EuroQol EQ-5D-5L. It consisted of five component scales, namely mobility, self-care, usual activities, pain, and anxiety. Recent evidence suggested that the newer 5-level version of the EQ-

5D had improved measurement properties, including feasibility, ceiling effects, sensitivity, and convergent validity [51]. The EQ-5D-5L had good test-retest reliability, as indicated by intraclass correlation coefficients (ICCs) ranging from 0.65 to 0.91 for the EQ-5D index [52].

### **Self-Assessment of Physical Activity Questionnaire (SAQ)**

Self-Assessment of Physical Activity Questionnaire (SAQ) will be used for physical capacity. The SAQ is a 13-item, self-administered activity questionnaire assessing common physical activities associated with personal care, ambulation, household tasks and recreation [53]. All these activities have a known metabolic equivalent (MET) obtained from the Compendium of Physical Activities. Each question required a 'yes' or 'no' response. A SAQ score will be obtained by recording the corresponding MET value of the most demanding activity that the participant perceived they could complete without symptoms [53]. All scores will be correlated against measured of peak oxygen consumption [53].

### **Fatigue Severity Scale (FSS)**

The Fatigue Severity Scale (FSS) is a method of evaluating the impact of fatigue. The Fatigue Severity Scale (FSS) is widely used to assess the impact of fatigue on daily functioning. Its psychometric properties have been evaluated in various populations, demonstrating its reliability and validity [54]. The FSS is a short questionnaire that requires patients to rate their level of fatigue. The FSS questionnaire contains nine statements that rate the severity of fatigue symptoms. Read each statement and circle a number from 1 to 7, based on how accurately it reflects the condition during the past week and the extent to which patients agree or disagree that the statement applies to patients [55].

### **The Global Rating of Change Scale**

This is a self-reported measure of patients' perceived change. It will be administered prior to the performance-based assessments preoperatively, prior to discharge, 4 weeks and 3 months postoperatively. Participants will be asked: 'Overall, how do your arms function now, compared with how your arms functioned at the initial assessment before surgery?' Responses will be recorded according to a 7-point scale from 'very much improved' to 'very much worse'. It has been previously reported that when participants rate their change as 'minimally improved', 'no change' or 'minimally worse', it is unlikely that a clinically important difference has occurred;

therefore, these patients are grouped into an ‘unchanged’ category [56]. Responses of ‘much worse’, ‘very much worse’, ‘much improved’ and ‘very much improved’ indicate a clinically important difference has occurred and therefore these patients are grouped into a ‘changed’ category [56].

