## **1.2 Research Questions**

- 1.21 What is the current practice amongst physiotherapists treating patients following major abdominal surgery in Malaysia?
- 1.22. What is the optimum prehabilitation program with a focus on exercise intervention to improve multidomain recovery following major abdominal surgery in Malaysia
- 1.23 How does a change in exercise intervention protocol (HIIT versus MICT) affect multidomain recovery that includes, cardiorespiratory fitness, respiratory muscle strength, physical function, pain and discomfort, psychological recovery, and health-related quality of life (HRQOL)?
- 1.24 What are the clinimetric properties (MCID) of selected pain, function and physical activity assessment tools used following major abdominal surgery in Malaysia

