### **Secondary Objectives**

- i) To assess the effect of HIIT over MICT on physical performances (Short Physical Performance Battery and 1 minute Sit to Stand), upper limb strength (Hand Grip Test) and body composition (Bioimpedance test), fatigue (Fatigue Severity Scale), psychological recovery (the Hospital Anxiety Depression Scale (HADS) and health related quality of life (EuroQoL).
- ii) To identify what is the type of exercise timing, dosing and content of prehabilitation
- iii) To determine the current practice among Malaysian physiotherapists on treating patients undergoing major abdominal surgery

- iv) To determine the clinometric properties of selected pain, function and physical activity assessment tools used following major abdominal surgery in Malaysia.

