## Statistical analysis

The analysis will follow the intention-to-treat, whereby all participants will be analyzed according to the groups to which they were originally randomized, regardless of their adherence to the intervention protocol. SPSS version 27.0 will be used to analyse all collected data. Missing data will be handled using multiple imputation, which creates several datasets by statistically estimating missing values and then combines the results to account for uncertainty. This method is preferred over last observation carried forward, as it reduces bias and more accurately reflects variability in clinical studies [61].

Descriptive statistics will summarize participants' baseline demographic and clinical characteristics. Continuous variables will be reported as mean (standard deviation, SD) or median (interquartile range, IQR) depending on the distribution, while categorical variables will be reported as frequency (percentage). Baseline comparability analysis of the clinical outcomes between groups will be performed using independent *t*-tests for continuous variables and Chi-square tests for categorical variables.

The primary outcomes (6MWT and MIP) and secondary outcomes (1MSTS, SPPB, hand grip strength, FSS, Bio-impedance Test, EuroQol, SAQ and Global Rating of Change Scale) will be measured at multiple time points: baseline, post-prehabilitation (4 weeks), before hospital discharge, and at 4 and 12 weeks postoperatively. To evaluate changes over time and between-group differences, a linear mixed-effects model (mixed model ANOVA) will be employed, provided the assumptions of normality and sphericity are met. Normality will be evaluated using the Kolmogorov–Smirnov test, while sphericity will be assessed using Mauchly's test. Mixed model ANOVA will provide results for time effect, group effect, and time-group interaction effect. Statistically significant time effect and group effect indicates significant within-group changes and between-group difference respectively, while significant time-group interaction effect determine if the interventions yield the desired effect on the dependent variables. Post hoc pairwise comparisons will be conducted using Bonferroni correction where appropriate.

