## Patient Identified Cardiac Pain Using Numeric And Visual Prompts

### Appendix C

#### Intensity of Chief Pain/Discomfort

How 'bad/distressing' is your pain/discomfort

Circle **ONLY** one number

[figure not shown]

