### *Global Rating of Change Scale*

How does your function now, compare to your function at the initial assessment before surgery?

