***MET = metabolic equivalent***

---

**Step 3:** Record the patient's age in years, height in centimetres and weight in kilograms.

**Step 4:** To calculate  $\text{VO}_2$ ; substitute these values into the following equation:

|                                                                                                                   |
|-------------------------------------------------------------------------------------------------------------------|
| $\text{VO}_2 = 2.36(\text{SAQ}) + 0.35(\text{HEIGHT cm}) - 0.19(\text{AGE yrs}) - 0.16(\text{WEIGHT kg}) - 33.89$ |
|-------------------------------------------------------------------------------------------------------------------|

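### Objective iv (MCID of pain, function and physical-activity tools) is poorly supported: the change anchor is worded two ways, the SAQ criterion is never measured, and no dedicated pain scale is scheduled

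*Protocol*

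**What the plan says.** Secondary objective iv reads "To determine the clinometric properties of selected pain, function and physical activity assessment tools used following major abdominal surgery in Malaysia". Its counterpart in section 1.2 names the property of interest: "What are the clinimetric properties (MCID) of selected pain, function and physical activity assessment tools used following major abdominal surgery in Malaysia". Question 1.23 also lists pain and discomfort among the recovery domains.

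- **Anchor.** In the body text (The Global Rating of Change Scale) the participant is asked "Overall, how do your arms function now, compared with how your arms functioned at the initial assessment before surgery". The form in the appendix asks instead "How does your function now, compare to your function at the initial assessment before surgery". Both use a seven-point scale.
- **Physical activity.** The SAQ section states: "All scores will be correlated against measured of peak oxygen consumption [53". In the appendix, Step 4 of the SAQ gives a formula for VO2 from the SAQ score, height, age and weight, with the instruction to "substitute these values into the following equation".
- **Pain.** The Statistical analysis section lists "secondary outcomes (1MSTS, SPPB, hand grip strength, FSS, Bio-impedance Test, EuroQol, SAQ and Global Rating of Change Scale", with no pain scale among them. The appendix holds a pain-intensity sheet headed "Patient Identified Cardiac Pain Using Numeric And Visual Prompts", which Fig. 1 does not schedule.

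**The concern.** An anchor-based MCID links change on a tool to the patient's own rating of change in the same construct. If the rating asks about arms, it says little about walking or leg function, which is what most of the function tools measure. If body text and form are used interchangeably, the answers are not to one question and should not be pooled.

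For the SAQ, the protocol states an analysis that the trial cannot carry out, because one of its two variables is never collected. Someone trying to honour the sentence might turn to the only VO2 on the forms, which is a function of the SAQ.

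For pain, a tool class is named in the objective and in two research questions without a dedicated instrument among the outcomes.

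All three concern what is asked and measured at the visits. A later analysis plan cannot recover answers to a question that was not put, or a measurement that was not taken.

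**Working it through.** The protocol gives no figure for this objective, so the check is mainly a comparison of sections, plus one short calculation.

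**1. Anchor against the tools it would serve**

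| Tool | What it measures (protocol) | Arm wording (body text) | Overall-function wording (appendix) |
|---|---|---|---|
| 6MWT | walking, functional capacity | no match | match |
| SPPB | lower-extremity performance | no match | match |
| One-minute sit-to-stand | functional status, exercise capacity | no match | match |
| Hand grip | upper-limb strength | match | general match |

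The two wordings cannot both be the question asked. No other global rating of change is described, so the choice decides which MCIDs can be estimated.

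**2. SAQ criterion**

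The outcome descriptions, the list in Statistical analysis and Fig. 1 contain no cardiopulmonary exercise test and no measured VO2. The only VO2 is the appendix formula:

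VO2 = 2.36(SAQ) + 0.35(height, cm) − 0.19(age, years) − 0.16(weight, kg) − 33.89

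Suppose this value replaced a measured one. With independent inputs, the correlation of the SAQ with its own VO2 is

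r = √[ (2.36·SD_SAQ)² / ( (2.36·SD_SAQ)² + (0.35·SD_height)² + (0.19·SD_age)² + (0.16·SD_weight)² ) ]

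The documents give no SDs. Assumed: height 8 cm, age 13 years, weight 13 kg. The fixed part of the denominator is 2.80² + 2.47² + 2.08² = 7.84 + 6.10 + 4.33 = 18.27.

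| Assumed SD of SAQ (MET) | (2.36·SD)² | Total | r |
|---|---|---|---|
| 1.2 | 8.02 | 26.29 | 0.55 |
| 1.8 | 18.05 | 36.31 | 0.70 |
| 2.5 | 34.81 | 53.08 | 0.81 |

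A moderate to high correlation would appear with no physiological measurement behind it. These values are illustrative. They depend on the assumed SDs and on independence, and they apply only if the calculated VO2 were substituted for a measured one.

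**3. Pain**

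No pain scale is described among the primary or secondary outcomes, listed for analysis, or scheduled in Fig. 1. The EQ-5D-5L, which has one five-level pain/discomfort item, is scheduled at baseline and at all four later assessments. The appendix pain sheet is not referred to in the outcome sections. Part of it is a figure that is not reproduced, so its full content cannot be judged.

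**The case against.** The strongest reply is that the objective survives in large part.

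- **Function.** If the appendix form is what participants complete, an anchor for the walking and lower-limb tools exists. Even the arm wording would serve hand grip. This stands, and it makes the first defect a contradiction to be resolved and not the absence of an anchor.
- **Physical activity.** Question 1.24 asks for the MCID. That needs change in the SAQ and a change rating, both of which are scheduled, and it does not need VO2. This also stands: the missing measurement defeats only the promised correlation. The protocol says measured VO2 and nowhere plans to substitute the calculated value, so circularity is a risk and not a stated analysis.
- **Pain.** The EQ-5D-5L item is collected at every assessment. That is true, but a single five-level item is thin support for the MCID of pain tools.
- **Importance.** This is the fourth secondary objective, and the HIIT versus MICT comparison on 6MWT and MIP does not depend on it. That limits the weight of the point.

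The reply does not remove the conflict between body text and form, the sentence describing an impossible analysis, or the lack of a dedicated pain scale.

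**Conclusion.** The point holds as one of poor support. The anchor is worded two ways, and the arm version fits hand grip only. The SAQ correlation names a measurement the trial does not take. Pain rests on one EQ-5D-5L item.

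Three stronger readings are tempting and are not supported:

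- A reader might infer that objective iv cannot be answered for any of its three tool classes. The appendix anchor, the fit of hand grip to the arm wording, the fact that an SAQ MCID needs no VO2, and the EQ-5D-5L pain item each contradict that.
- A reader might infer that the arm wording fails because resistance training is matched between the groups. An MCID is estimated from change within patients and needs no difference between groups, so the matching is irrelevant.
- A reader might infer that a weaker anchor shrinks the MCID in proportion to its correlation with the outcome. Under a linear model the mean change at anchor level z is μ + rσz. That is proportional to r only if the overall mean change μ is zero, which is implausible across training and major surgery. The protocol also states no MCID method, so no shrinkage factor can be given.

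The damage is confined to a secondary objective and to the Global Rating of Change as a secondary outcome. Its extent depends on which wording participants have been asked, and the documents do not say. It should be corrected, because anchor data collected under the wrong wording cannot be repaired later.

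**What to change.** 1. **Anchor.** In The Global Rating of Change Scale, replace the arm question with the appendix wording on overall function, for use at every visit after baseline. Record which wording each participant has already been asked, and do not pool arm-worded answers in the anchor analysis.
2. **SAQ.** Delete the peak-VO2 sentence, or name a criterion the trial does collect, for example 6MWD at the same visit. State that VO2 calculated from the appendix equation is not a criterion for the SAQ.
3. **Pain.** In questions 1.23 and 1.24 and objective iv, either limit the pain part to the EQ-5D-5L item or drop it. Alternatively, describe the existing appendix pain item as an outcome, give it a title suited to abdominal surgery and schedule it in Fig. 1.

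The cost is an amendment to protocol and form wording, plus one short pain question per visit if the last option is chosen. The real downside is lost anchor data from anyone already asked about arms. Recruitment of 70 participants runs from February 2025 to July 2026, so that loss could be small or substantial; its size is unknown.

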## **Bio-electrical Impedance Analysis**

An InBody device utilizing Bio-electrical Impedance Analysis will be used to assess body composition by estimating key components such as lean body mass, fat mass, and total body water. This method involves passing a low-level electrical current through the body and measuring the resulting impedance to estimate body composition parameters, including total body water, extracellular water, intracellular water, fat mass, fat-free mass, body fat percentage, and bone mineral content [57].

Bioelectrical Impedance Analysis has been validated as a reliable method for assessing body composition, showing strong correlations with CT-derived measurements of torso fat volume and waist fat area, with correlation coefficients ranged from 0.86 to 0.95 in both men and women ( $p < 0.001$ ) [58]. InBody devices showed a 98% correlation with dual-energy X-ray absorptiometry (DXA), with strong agreement across all body mass index (BMI) categories [59]

## **Adherence monitoring**

Data related to exercise prescription, progression, complaints, injuries, and symptoms during training sessions for the both groups will be systematically recorded. Participants will be encouraged to adhere to the exercise guidelines outlined in their weekly flyers. Attendance will be documented, including the total number of sessions attended and successfully completed. Detailed reasons for incomplete sessions or participant dropouts will be recorded to evaluate non-compliance. Adherence to the prehabilitation exercise program will be closely monitored, alongside compliance with the prescribed exercise regimen. Additionally, participants will be asked to report the duration of their adherence and rate their adherence to home-based activities using a numerical scale [60].

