#### **1.5 Expected Outcome and Benefit**

Findings from this study will warrant its application to every prehabilitation patient who undergoes major abdominal surgery:

- i. Aerobic training, resistance training and respiratory training might help the patient to improve physical performance and quality of life before the operation.
- ii. Prehabilitation exercise might help patients to recover faster by reducing the length of stay and reducing the rate of PPC and mortality.
- iii. The results of the present study will help physiotherapists to extend the protocol and improvise the protocol if necessary.
- iv. First RCT with robust methodology in Malaysia and worldwide
- v. the outcomes of this study inform the implementation of clinical and regulatory guidelines on prehabilitation based on the Malaysian model for patient and community safety; quality of life and standards of care of individuals scheduled for MAS surgery
- vi. This research could influence the prehabilitation protocol and exercise recommendations for abdominal surgery by emphasizing the importance of precise exercise dosage.

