## **Blinding and allocation**

Patients and outcome assessors, will remain blinded to treatment allocation. However, the treating physiotherapists cannot be blinded due to the nature of the intervention. To maintain blinding, details of the intervention will not be recorded in the medical records. Outcome assessments will be conducted by a blinded assessor based off-site from the outpatient department, ensuring impartiality in both inpatient and outpatient settings. Intervention sessions will occur on different days from those scheduled for outcome assessments to further reduce the risk of unblinding. If a participant from the intervention group discloses details of their intervention to the assessor, this will be documented and reported, with the rationale recorded. All analyses will be performed on an intention-to-treat basis once randomization is unblinded.

Following recruitment and baseline assessments, participants will be randomly assigned to one of two groups which will be control group (MICT) or the intervention group (HIIT) using a computer-generated random number sequence. Allocation will be conducted by an independent individual utilizing a block randomization method (5 blocks of 14). An administrative assistant, independent of the trial, will prepare 70 sequentially numbered opaque envelopes, each containing a group allocation. A physiotherapist, trained in the study protocol, will deliver the intervention. Participants in the control group will receive moderate-intensity continuous training (MICT), while those in the intervention group will engage in high-intensity interval training (HIIT) preoperatively. Both groups will commence and conclude sessions with a warm-up and cool down to mitigate the risk of adverse events.

This study is will be conducted at a teaching hospital of the Hospital Canselor Tuanku Muhriz, Malaysia. Prospective consecutive patients will be invited to participate in the study prior to elective major abdominal surgery from February 2025 to July 2026. Fig 2 summarises the design of the trial, and each of the trial's aspect is described in detail below.

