### **Standard Care for Control Group (MICT)**

This will be a tailored and supervised by a single physiotherapist (more than 10 years clinical experiences in cardiorespiratory) in outpatient hospital setting. Participants will engage in an aerobic (moderate intensity continuous training), strengthening exercise and inspiratory muscles training program prior to the date of their surgery.

For aerobic exercise this will be a low intensity in week one with graduation to moderate intensity. Moderate intensity continuous training (MICT) will allow 55-75% of maximum heart rate (MHR) [33]. Aerobic exercise training (eg: treadmill, cycling, walking exercise) 1-3 times per week (60 minutes) for overall duration typical 2-4 week prior to date of surgery. Patients' Maximum Heart rate (210-age) and Karvonen Formula will be used for targeted heart rate. Patients' heart rate will be monitored along the aerobic training using smart watch. However, the Karvonen formula may not be suitable for all patient populations, particularly those on beta-blockers or with underlying cardiac conditions. In such cases, training intensity will be guided the RPE between 10-13 RPE score, and appropriate modifications will be made to ensure safety. This approach allows for individualized intensity adjustment while maintaining the safety and effectiveness of the intervention.

For the progressive resistance exercise, the following muscle groups will be targeted: biceps brachii, triceps brachii, pectoralis major and minor, latissimus dorsi, deltoid and rhomboids using free weights. The intensity will be 70-80% of estimated 10 repetitions

maximum. The load not provided joint pain or severe muscle fatigue and/or arm fatigue on RPE of 10-13 on 6-20 RPE score [60]. Aim for a total session duration of about 45-60 minutes, including warm-up and cool-down. This includes 30-45 minutes of MICT, depending on the patient's tolerance. Sessions will be done 1-3 times per week [60].

In addition to the PVC weighted bar, we also used different types of resistance training such as band, dumbbells, kettlebells. Inspiratory muscles training will be given 20 mins per day with 30% of maximum inspiratory pressure (MIP) [14].

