#### **3.3 Data Management and Quality**

Data will be managed using an Excel database and SPSS version 27.0. Thorough training will be provided to all personnel involved in data collection, entry, and verification to ensure accuracy and consistency across measurements and to identify missing data. Regular checks will be performed to detect any inconsistencies within and between datasets. Data entry, security, and storage will follow strict protocols to ensure quality and confidentiality. All data will be encrypted and stored in a password-protected system with limited access, complying with privacy regulations. Additionally, two independent clinical members will serve in an advisory role to the clinical investigators, overseeing participant withdrawals, monitoring ethical conduct, and reviewing any serious adverse events.

Access to the final trial dataset will be limited to the principal investigator and designated members of the research team. There are no contractual agreements restricting the investigators' access to the data, and neither the sponsor nor the funder will have access to the raw dataset. This ensures the research team's full independence in data management, analysis, and reporting. The complete trial protocol is publicly available via the ANZCTR registry, and the raw dataset will be made available upon reasonable request and approval by the principal investigator. Process evaluation findings will be published in peer-reviewed journals and presented at relevant academic conferences.

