**ETHICAL APPROVAL TO CONDUCT RESEARCH IN THE NATIONAL UNIVERSITY OF MALAYSIA**

Research title       : The Effectiveness Of High-Intensity Interval Training Versus Moderate Intensity Continuous Training In Prehabilitation Among Patients Undergoing Upper Abdominal Surgery

Ethics Ref. No.       : JEP-2024-527

Approval period      : 06 November 2024 – 05 November 2026

Study Site            : Hospital Canselor Tuanku Muhriz

Sample Size          : 74 for Web Survey  
                          60 for RCT

With reference to the above.

2. The Research Ethics Committee, The National University of Malaysia (RECUKM) has provided ethical approval for above study. Please be reminded permission from the Deputy Dean of research of the faculty or Director of Institute/Centre and all relevant heads of departments / units where the study will be carried out must be obtained prior to the study. You are required to follow and comply with their decision and all other relevant regulations.

3. Please note that the investigator's responsibility is to ensure that:

- i. All Adverse Events should be reported to RECUKM as soon as possible.
- ii. Progress report should be submitted every **6 Months**.
- iii. All changes / amendments to the study documents / study sites / study team must be notified to the RECUKM. All changes must be approved by RECUKM before continuation of the study.
- iv. Application for renewal of the approval has to be submitted to RECUKM within one month (1 month) prior to the expiry of ethical approval.
- v. Final Report should be provided to RECUKM when the project is complete.
- vi. Please take note that all records and data are to be kept strictly **CONFIDENTIAL** and can only be used for the purpose of this study. All precautions are to be taken to maintain data confidentiality.

Required forms can be obtained from the The Research Ethics Committee, The National University of Malaysia (RECUKM) website: <https://www.ukm.my/jepukm>

Thank you.

[figure not shown]

UNIVERSITI KEBANGSAAN MALAYSIA  
*The National University of Malaysia*

---

SEKRETARIAT ETIKA PENYELIDIKAN UKM • UKM RESEARCH ETHICS SECRETARIAT

Yours sincerely,

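### Routine harm collection is described only for training sessions, so non-serious or delayed events between sessions, before surgery and during follow-up have no stated way of being found

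*Protocol*

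**What the plan says.** **Routine collection.** Harms appear under Adherence monitoring (Phase 2), where "complaints, injuries, and symptoms during training sessions for the both groups will be systematically recorded". For exercise away from the clinic, the same section asks participants how long they adhered and has them "rate their adherence to home-based activities using a numerical scale". It does not ask about symptoms or events there.

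**Exposure outside sessions.** Both arms receive inspiratory training; the control-arm section says "Inspiratory muscles training will be given 20 mins per day", and the HIIT section gives the same training. Both arms also receive a handout for continued aerobic and strength exercise with a carer's help. Sessions take place 1 to 3 times a week in the intervention sections, and twice a week in the Abstract.

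**Schedule.** Fig. 1 lists two primary and nine secondary measures. It has no row for adverse events or complications.

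**Provisions that reach beyond sessions.**
- Section 3.3 gives two independent clinicians the task of "monitoring ethical conduct, and reviewing any serious adverse events".
- Data collection (Phase 2) takes perioperative variables from participants and their charts, without itemising them.
- Statistical analysis uses respiratory complications as the outcome of an exploratory logistic regression.

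**Ethics condition.** Condition 3.i of the approval letter reads "All Adverse Events should be reported to RECUKM as soon as possible". Both later amendment letters ask again for adverse-event reports.

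**The concern.** An event is found only if someone asks about it or has a duty to record it. Under this protocol, routine asking is described for the session itself. An exertional symptom the next day, a strain from home resistance work, or a problem between the last session and the operation has no described route into the trial data unless it is serious. Even then, the route by which it reaches the advisers is not given.

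Two things are at stake. The first is compliance: the ethics condition has no restriction to sessions, so collection that has one cannot reliably meet it. The second is the comparison of arms. The trial is meant to shape exercise recommendations, and Section 1.5 speaks of "prehabilitation based on the Malaysian model for patient and community safety". If HIIT and MICT differ in delayed symptoms and not in what happens during the hour, the data would not show it.

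The July 2025 amendment widened the population by removing the 300 m walk threshold and the upper age limit of 75. Harm collection is not among the changes listed in that letter.

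**Working it through.** The protocol states no figure on this point, so there is none to reproduce. The check sets each period beside what is stated for it.

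| Period | What the protocol states | Would a non-serious event be found? |
|---|---|---|
| During sessions, both arms | Complaints, injuries, symptoms; attendance and vital signs | Yes |
| Between sessions, including home activity | Duration of adherence and an adherence rating | No stated step |
| Last session to surgery | Preoperative outcome tests and questionnaires; variables not itemised | No stated step |
| Surgery to discharge | Variables not itemised; respiratory complications needed for the regression | Partly |
| Discharge to 3 months | Outcome tests and questionnaires at 4 weeks and 3 months | No stated step |
| Any time, serious events only | Review by two advisers (Section 3.3) | Not covered; no detection step for serious events either |

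**Step 1: scope against the ethics condition.** The condition covers all adverse events with no limit of time or place. The routine collection covers one row of the table in full and one in part. The remaining periods depend on spontaneous report.

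**Step 2: days between sessions.** At 1 to 3 sessions a week, 7 − 3 = 4 to 7 − 1 = 6 days of each programme week have no session. At the Abstract's two sessions, it is 7 − 2 = 5 days. Inspiratory training is daily, so some prescribed training falls on days with no stated harm question, unless it is done only under supervision. These are calendar days and not a share of harms missed.

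**Step 3: can the share of exercise outside sessions be computed?** Only by assuming where inspiratory training is done and leaving out home aerobic and strength work, for which no volume is given.
- Low end: three 60-minute sessions (upper end of the MICT section) give 180 min. Inspiratory training at home on the other four days gives 4 × 20 = 80 min. Share = 80 / (80 + 180) = 31%.
- High end: one 20-minute session (lower end of the HIIT section) gives 20 min. Inspiratory training at home on all seven days gives 140 min. Share = 140 / (140 + 20) = 88%.

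A range of 31% to 88% settles nothing, so the point does not rest on it.

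**Step 4: contacts already available.** There are four face-to-face assessments after baseline (preoperative, before discharge, 4 weeks, 3 months), besides every session. All are in the plan now, and none carries a question about adverse events.

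**The case against.** The strongest reply is that the protocol does look beyond sessions. Any serious event goes to two independent reviewers, postoperative variables are taken from participants and charts, respiratory complications must be collected for the regression, and reasons for incomplete sessions and dropout are recorded. The ethics letter places a reporting duty on the investigator, and nothing in the protocol says that events outside sessions will go unreported. The phrase about sessions might also be read as qualifying only symptoms.

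Much of this stands. It rules out saying that harms are collected nowhere else, or that the protocol flatly contradicts the ethics letter. It does not supply a way of finding events. Review begins once an event is known; unitemised variables are not a harm question; and respiratory complications do not cover injury, exertional symptoms or the interval to surgery. The narrower reading of the phrase about sessions is possible, but the sentence sits in a section about what is recorded for training.

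The analysis of harms may sit in a statistical analysis plan that is not shown, so its absence here is not part of the point. The collection window and method belong in the protocol.

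Some stronger readings are tempting and are not supported:
- **That most exercise is done at home.** The documents do not say so, and the 31% to 88% range cannot decide it. It is driven by inspiratory training, whose place is not stated.
- **That there would be almost no safety data.** The high-intensity intervals are described only within sessions, where harms are recorded in both arms.
- **That the rule that "details of the intervention will not be recorded in the medical records" prevents events from being linked to training.** It withholds intervention details only. Session checklists are a separate source, and changing the rule would trade against blinding.

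**Conclusion.** The point holds as a should-fix: a cheap improvement to safety ascertainment. Routine harm collection is described for sessions only, and non-serious or delayed events between sessions, before surgery and after discharge have no stated means of detection. That is narrower than the ethics condition and leaves the harm comparison between HIIT and MICT incomplete.

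The size cannot be given as a number of missed events, because the protocol contains no event rates. Two figures a reader might reach for do not measure the defect. Session days as a share of all days from baseline to 12 weeks (from 2/119 = 2% to 12/112 = 11%) count calendar time, including 84 days after surgery. The one-sided 95% upper bound with no events in 35 patients, 1 − 0.05^(1/35) = 8.2%, is a limit of the sample size that remains after the fix.

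The conclusion assumes that the session wording applies to complaints, injuries and symptoms alike, and that no separate adverse-event procedure exists outside the protocol.

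**What to change.** Amend Adherence monitoring and Fig. 1 as follows.

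1. Record adverse events in both arms from randomisation to the 3-month visit.
2. Ask one neutral, open question at every session, covering the days since the previous one, and at each of the four existing follow-up assessments. Use the same wording in both arms.
3. Add one adverse-event row to Fig. 1.
4. State the route: events go to the two advisers in Section 3.3 and to the ethics committee under condition 3.i.
5. Tabulate events by arm.

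The cost is protocol wording, one schedule row, one question on existing forms and an amendment submitted to the ethics committee. It takes a few minutes per contact. The drawback is a small risk that an answer reveals the arm to the blinded assessor; asking after the outcome tests are finished would reduce it. Participants who have already passed a visit cannot be asked again on the same footing, so the report should state the date from which the new collection applied.
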